### Study duration

There is no specified end date for the research platform. It is anticipated that PLATINUM C will continue to enrol participants and integrate the testing of new interventions and/or groups of interventions until one of the following occurs:
The effectiveness and/or cost-effectiveness of all possible interventions are known and there are no new interventions to evaluateChronic HCV infection is no longer deemed to be a public health problemFunding or other necessary support is no longer available

Should the platform be stopped, the end of this study is the date of the last scheduled follow up for any participant.

### Study procedures

#### Informed consent

A participant must provide informed consent (written or electronically) before any specific procedures are performed or data collected. Electronic and/or written versions of the participant information sheet will be presented to the participant detailing no less than: the exact nature of the project; what it will involve for the participant; the implications and constraints of the protocol; any risks involved in taking part. It will be clearly stated that participation is voluntary.

#### Withdrawal of participants

Participants have the right to withdraw from this study at any time without penalty or loss of benefits. Data obtained prior to participants’ withdrawal from the study will be included in the analysis.

#### Data collection

Relevant data (outlined in Table 1) will be obtained directly from the healthcare providers and participants. Data will be collected through data capture and prescribing tools and phone and/or email participant surveys.

**Table 1 Tab1:** Summary of data collection

Data type	Information recorded	Time point
Demographics	Age, gender, postcode, Indigenous status	Enrolment
Lifestyle	Self-reported injecting drug use, self-reported alcohol in-take, self-reported housing status, self-reported reuse of a needle/syringe, self-reported prescribed opioid substitution therapy, risk of treatment disruption (including imprisonment)	Enrolment
Clinical	Hepatitis C history, previous treatment, comorbidities, HCV genotype and RNA level, liver function tests, liver fibrosis assessment	Treatment prescription
Treatment	DAA therapy and duration prescribed, treatment setting, type of prescriber, concurrent medication, other concurrent HCV management interventions	Treatment prescription
Medication adherence	Self-reported adherence to therapy	Weekly during treatment course
Quality of life	Self-reported quality of life (QoL) score (EQ-5D-5L)	0, 3, 6, 12 and 24 months after treatment initiation
Outcomes	HCV RNA PCR, all re-collected laboratory and imaging results, self-reported injecting drug use,	3 months after treatment completion

PLATINUM C will use a direct data capture tool that is integrated with the practice software (described in Fig. 1). Data from consenting participants will be extracted and uploaded to the data capture system. Information unable to be extracted with be uploaded by the consulting practitioner. The data capture tool will ensure all information required for prescribing DAAs or referral for specialist consultation is collected. The data capture tool will also serve to provide prescribing recommendation based on the Australia recommendation for genotype, cirrhosis level and treatment experience. Patient information collected will be stored within the practice software and de-identified participant information will be fed directly into a secure online database via secure middleware. A monitoring dashboard will allow healthcare staff to track when participants are due for follow-up SVR12 testing and long-term cirrhosis assessments.

**Fig. 1 Fig1:**
[figure not shown]
Study workflow and utilisation of the data capture tool

Data will be stored on a password protected electronic database housed securely on a server at the Telethon Kids Institute in Perth, Western Australia, and will be archived until 15 years after the end of enrolment or publication, whichever is later.

##### Baseline and clinical outcome assessment

Prospective baseline, treatment and outcome data collection will be integrated into standard clinical care. This information is currently routinely required in the management of hepatitis C in Australia as per standard guidelines from the Gastroenterological Society of Australia and Australian Liver Association [9]. Embedding of data collection of clinical information will be facilitated by a HCV prescribing tool.

##### Life-style questionnaire

Participants will be asked to complete a questionnaire (see Additional file 1) to further characterise risk behaviours, treatment responses and healthcare utilisation across different patient groups including among marginalised groups who are traditionally underserved by the healthcare system. These questionnaires were developed in consultation with the Platinum C Community Reference Group.

##### Adherence monitoring

Participants will be invited to self-report medication adherence. Upon initiation of HCV antiviral therapy, participants who opt-in will receive either a weekly phone or text message asking them to provide the number of doses taken in the preceding 7 days.

##### Quality of life questionnaire

The self-reported EQ-5D-5L quality of life instrument [10] will be issued electronically to those who opt-in at 0, 3, 6, 12 and 24 months after initiation of DAA therapy.

#### Data analysis

Primary analyses of all data will use the intention-to-treat (ITT) principle. Demographic, clinical and other baseline variables will be summarised by viral genotype, liver cirrhosis status, previous HCV treatment and clinician prescribed treatment. Continuous variables will be summarised as mean and standard deviation for symmetric distributions and median and interquartile range (IQR) for asymmetric distributions. Categorical variables will be summarised at each level as frequency and percentage. Frequencies below five will be reported as “< 5” to protect individual confidentiality.

For the primary endpoint a Bayesian logistic regression model, with weakly informative priors, will be used to compare treatment groups and incorporate Bayesian borrowing across pre-specified subgroups. The exact model will depend on the trial modules (and interventions) defined and will be documented in the statistical analysis plan (SAP). The proportion of participants that achieve SVR12 will be reported every 200 participants. Secondary endpoints will be similarly summarised and analysed using Bayesian regression models, which will be documented in the SAP.

Self-reported DAA treatment adherence will be summarised as the median (and IQR) proportion of prescribed doses taken in weeks 1 to 12 by viral genotype, liver cirrhosis status and clinician prescribed treatment. Self-reported quality of life measured during and for up to 24 months after initiation of treatment, as measured by the EQ-5D-5L, will be summarised by median (and IQR) by viral genotype, liver cirrhosis status and clinician prescribed treatment.

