### Objectives

The primary objective of PLATINUM C is, for adults with chronic HCV infection, to determine the absolute and comparative effectiveness of a range of interventions to achieve a HCV virological cure. This is demonstrated by a sustained viral response (SVR), defined as an undetectable HCV ribonucleic acid (RNA) ≥12 weeks after discontinuation of antiviral treatment and within 18 months of the start of treatment. Interventions will include licenced and funded DAA therapies and other management strategies to be defined by platform embedded trials.

The secondary objectives are to describe chronic HCV management in primary care for different patient subgroups, including by: (i) describing the distribution of the treatment response under alternative management options, (ii) characterising treatment adherence, (iii) identifying demographic and clinical characteristics associated with high risk of lost-to-follow-up from standard care, and (iv) describing and comparing patterns of health care utilisation.

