### Outcomes

The primary outcome is virological cure as evidenced by the endpoint of sustained virological response (SVR) defined as a negative HCV RNA (in plasma) PCR result 6 to 18 months after the initial prescription of DAA therapy and no less than 12 weeks after the end of antiviral treatment.

Secondary outcomes and endpoints are:
(i)Completion of follow up defined by the completion of SVR12 testing (HCV RNA PCR)(ii)Adherence of study participants to antiviral treatment recorded as the self-reported proportion of total prescribed doses taken,(iii)Quality of life, as measured by the self-reported EQ-5D-5L questionnaire administered during and for up to 24 months after initiation of treatment and,(iv)Healthcare utilisation defined as any attendance for healthcare related service that attracts a cost to the individual, insurer or government.

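### The weeks 1 to 12 adherence summary does not match the whole-course adherence endpoint and drops doses after week 12

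*Protocol article*

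**What the plan says.** Secondary outcome (ii) in the Outcomes section is "Adherence of study participants to antiviral treatment recorded as the self-reported proportion of total prescribed doses taken". It carries no week limit.

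Table 1 in the Data collection section schedules the adherence item "Weekly during treatment course", again without a cap, and records "DAA therapy and duration prescribed" for each participant. The Adherence monitoring section describes a weekly contact from the start of therapy, for those who opt in, "asking them to provide the number of doses taken in the preceding 7 days".

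The Data analysis section sets the summary: "Self-reported DAA treatment adherence will be summarised as the median (and IQR) proportion of prescribed doses taken in weeks 1 to 12", reported "by viral genotype, liver cirrhosis status and clinician prescribed treatment". It gives no rule for a course that runs past week 12. Prescribed duration is not among the reporting groups.

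No course length in weeks appears anywhere in the article, and nothing says that every course lasts 12 weeks. The Objectives section keeps the range of regimens open: "Interventions will include licenced and funded DAA therapies and other management strategies to be defined by platform embedded trials".

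**The concern.** The outcome definition and the collection schedule both refer to the whole course, while the summary stops at week 12. A participant whose dosing continues beyond that point contributes only part of the data that define the endpoint. Non-adherence late in treatment, which a weekly record is well placed to show, would not appear in the reported figure.

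Characterising adherence is a named secondary objective, so the reported number should be the defined one. A reader of the results would also be unable to see the truncation, because duration is not a reporting group.

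**Working it through.** The protocol gives no adherence figure and no course length, so there is no stated number to reproduce. The check compares the endpoint with the summary for illustrative courses.

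**Inputs from the protocol.** Endpoint: doses taken out of total prescribed doses (Outcomes). Summary window: weeks 1 to 12 (Data analysis). Collection: weekly over the course (Table 1).

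**Assumptions, not in the protocol.** One dose a day; course length L of 8, 12, 16 or 24 weeks; no interruption; adherence a1 in weeks 1 to 12 and a2 afterwards.

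**Step 1: doses outside the window.** Total doses = 7 × L. Doses inside = 7 × min(L, 12). Doses outside = 7 × max(L − 12, 0).

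| L (weeks) | Total | Inside | Outside | Share ignored |
|---|---|---|---|---|
| 8 | 56 | 56 | 0 | 0% |
| 12 | 84 | 84 | 0 | 0% |
| 16 | 112 | 84 | 28 | 28/112 = 25% |
| 24 | 168 | 84 | 84 | 84/168 = 50% |

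**Step 2: endpoint against summary.**

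- Endpoint = (inside × a1 + outside × a2) / total.
- Summary, reading A (doses taken in weeks 1 to 12 over doses prescribed for those weeks) = a1.
- Summary, reading B (doses taken in weeks 1 to 12 over total prescribed doses) = inside × a1 / total.

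Reading A is the natural one. The sentence does not exclude B.

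| L | a1, a2 | Endpoint | A | B |
|---|---|---|---|---|
| 8 | 95%, none | 95% | 95% | 95% |
| 12 | 95%, none | 95% | 95% | 95% |
| 16 | 95%, 95% | 95% | 95% | 71.25% |
| 16 | 95%, 70% | (79.8 + 19.6)/112 = 88.75% | 95% | 71.25% |
| 16 | 95%, 0% | 79.8/112 = 71.25% | 95% | 71.25% |
| 24 | 95%, 95% | 95% | 95% | 47.5% |
| 24 | 95%, 70% | (79.8 + 58.8)/168 = 82.5% | 95% | 47.5% |
| 24 | 95%, 0% | 79.8/168 = 47.5% | 95% | 47.5% |

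Up to 12 weeks, both readings equal the endpoint. Beyond 12 weeks, reading A equals it only if adherence does not change after week 12. Reading B equals it only if no dose is taken after week 12, and it caps a fully adherent participant at 84/112 = 75% or 84/168 = 50%.

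**Step 3: interruption.** In a 12-week course, each week of pause after which the course is resumed and completed moves 7 of 84 doses (8.3%) past week 12. The endpoint counts those doses and the window does not.

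**The case against.** The strongest reply is that this sentence is one descriptive median and IQR, not a redefinition of the endpoint. The regression models for secondary endpoints are left to the SAP, which is not shown and may analyse the whole course. Weekly data are collected throughout, so nothing is lost, and a common early window can be a legitimate summary. Part of this stands: the point should not be read as saying that every adherence analysis is truncated. But the deferral covers the models. The window is stated in the protocol itself, without qualification, and is not presented as a separate early measure.

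Three stronger inferences are tempting, and the protocol does not support them:

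- *Shorter courses are also misreported.* A fully adherent 8-week participant would score 56/84 = 67% only with a fixed 84-dose denominator. The sentence refers to prescribed doses, so weeks with none prescribed add nothing.
- *A late start pushes doses out of the window.* The Adherence monitoring section starts the weekly contacts when therapy begins. If week 1 is counted from there, a late start has no effect; only an interruption does.
- *Truncation distorts the contrast between cirrhosis or treatment groups.* The Background says that guidelines take genotype, cirrhosis and previous treatment into account, but it does not link them to duration. Uneven truncation is a plausible inference and is not shown.

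It is also fair to say that a participant who stops completely at week 12 is an extreme case, and that a group median may move far less than one person's figure.

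**Conclusion.** The mismatch is real but narrow. The Data analysis window does not measure the endpoint in the Outcomes section once dosing passes week 12. For such participants it omits 25% of doses (16 weeks) or 50% (24 weeks), assuming one dose a day and those course lengths. On the natural reading, a fall from 95% to 70% adherence after week 12 is reported as 95%, where the endpoint is 88.75% or 82.5%.

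How many participants this concerns cannot be determined from the protocol, and the number could be small. The consequence is minor: the outcome is secondary, self-reported, opt-in and summarised descriptively, and the primary SVR analysis does not depend on it.

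**What to change.** In the adherence sentence of the Data analysis section, replace the limit to weeks 1 to 12 with *over each participant's full prescribed course*. State that the denominator is that participant's total prescribed doses, taken from the recorded regimen and duration. Count all doses reported until the course ends, including those taken after an interruption. If a 12-week figure is still wanted, keep it as a separately labelled early-adherence summary.

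The cost is one sentence. Table 1 already provides for weekly adherence over the course and for the prescribed duration, so no new data are needed.

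### The named adherence summary, median and IQR of a proportion capped at 100%, can hide non-adherence affecting fewer than about a quarter of a group (minor)

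*Protocol article*

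**What the plan says.** All places are in the protocol article.

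- **Outcomes** defines the secondary endpoint: "Adherence of study participants to antiviral treatment recorded as the self-reported proportion of total prescribed doses taken". A proportion of this kind is bounded at 0% and 100%.
- **Objectives** lists, as a secondary objective, "ii) characterising treatment adherence".
- **Data analysis** names the summary: "Self-reported DAA treatment adherence will be summarised as the median (and IQR) proportion of prescribed doses taken", for weeks 1 to 12, by viral genotype, cirrhosis status and prescribed treatment. It names no mean, lower percentile or percentage below a threshold.
- **Data analysis** also states: "Secondary endpoints will be similarly summarised and analysed using Bayesian regression models, which will be documented in the SAP". The descriptive table is therefore not the only planned analysis of adherence.
- **Adherence monitoring** describes the raw data: participants who opt in report, each week, how many doses they took in the past seven days.

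**The concern.** Objective (ii) is descriptive, so the descriptive table is a large part of its answer. What one wants from it is how many people fall short, by how much, and in which subgroups. A median and two quartiles give that poorly when values pile up at an upper bound. Once more than three quarters of a group sit at the bound, all three numbers equal the bound, whatever happens among the rest.

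The article says that observed variation will inform the design of embedded trials (Study design) and names treatment completion as needing better strategies (Abstract, Discussion). A table that prints the same entry for a subgroup with one participant in twenty non-adherent and one with nearly one in four would be of little help in choosing where to look.

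**Working it through.** The article states no adherence rate, distribution or sample size, so there is no figure of its own to reproduce. What follows is an illustration.

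**Inputs**
- From the article: adherence is a proportion with maximum 100%; the summary is median (IQR).
- Borrowed from the article for scale only: a group of 200, the interval at which SVR12 is to be reported. Real subgroups may be smaller.
- Assumed: a share f of the group takes 60% of prescribed doses and the rest report 100%.

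**Step 1: what the summary prints.** The median is 100% when f is below 50%. The first quartile, and so the whole IQR, is 100% when f is below 25%. The mean is 1 − f × (1 − 0.60) = 1 − 0.40f.

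| f | Number of 200 | Median (IQR) | Mean |
|---|---|---|---|
| 5% | 10 | 100% (100–100) | 1 − 0.020 = 98.0% |
| 10% | 20 | 100% (100–100) | 1 − 0.040 = 96.0% |
| 20% | 40 | 100% (100–100) | 1 − 0.080 = 92.0% |
| 24% | 48 | 100% (100–100) | 1 − 0.096 = 90.4% |
| 30% | 60 | 100% (60–100) | 1 − 0.120 = 88.0% |
| 49% | 98 | 100% (60–100) | 1 − 0.196 = 80.4% |

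The first four rows cannot be told apart by the planned summary. The last two can be told from the first four, but not from each other.

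The 60% figure is not critical. With non-adherers at 50% of doses, the entry is again 100% (100–100) from f = 5% to 24%, while the mean falls from 97.5% to 88%.

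**Step 2: chance that the quartile reveals anything.** In a sample of 200, the first quartile is below 100% under any usual quartile convention once at least 51 participants are non-adherent (at exactly 50 it depends on the convention). With X binomial (200, true share):

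| True share | P(X ≥ 51) |
|---|---|
| 15% | 0.0001 |
| 20% | 0.03 |
| 25% | 0.46 |
| 30% | 0.93 |
| 40% | about 1 |

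**Step 3: relaxing the ceiling assumption.** Suppose instead that the majority miss occasional doses: 84 doses, each taken with probability 0.99, 0.97 or 0.95 (all assumed). One simulated group of 200 was used per row, with 15% or 20% then set to half their doses.

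| Per-dose probability | First quartile: 0% → 15% / 20% affected | Mean: 0% → 15% / 20% affected |
|---|---|---|
| 0.99 | 98.8% → 97.6% / 97.6% | 99.0% → 91.7% / 89.2% |
| 0.97 | 96.4% → 95.2% / 94.0% | 97.2% → 90.1% / 87.8% |
| 0.95 | 94.0% → 91.7% / 91.7% | 94.9% → 88.2% / 85.9% |

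The quartile now moves, but by only about 1 to 2.5 points, against a fall of about 7 to 10 points in the mean. The insensitivity is reduced but does not disappear.

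**The case against.** **The table is not the whole analysis.** A Bayesian regression of secondary endpoints is planned, and its form is left to a SAP that is not shown. This stands. It rules out saying that the registry cannot detect differences in adherence. It does not change the descriptive summary that the article itself names.

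**Median and IQR follow the article's general rule for asymmetric variables.** True, and the rule is reasonable for skewed data. It works less well for values stacked at a bound, where quartiles can coincide.

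**The distribution is assumed.** This stands, and the conclusion is conditional on it. Opt-in self-report may push answers towards the ceiling, but that is inference.

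A reader might be tempted by two stronger claims.

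- *The summary cannot show non-adherence in any minority.* It can. Shares of roughly 25% to 50% lower the first quartile, as Steps 1 and 2 show.
- *The EQ-5D-5L summary, "as measured by the EQ-5D-5L, will be summarised by median (and IQR"), has the same fault and undermines cost-effectiveness work, since Study duration lists as a stopping condition "The effectiveness and/or cost-effectiveness of all possible interventions are known".* The article does not support this. It gives no EQ-5D-5L distribution that would show a ceiling. Even in an invented case with affected participants at 0.6 and the rest at 1.0, groups with 20% and 45% affected print as 1.0 (1.0–1.0) and 1.0 (0.6–1.0), so the IQR separates them. No cost-effectiveness objective, outcome or analysis is stated. Individual scores are collected at 0, 3, 6, 12 and 24 months, so quality-adjusted life years could be computed later whatever descriptive median is reported.

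**Conclusion.** The point holds in a narrow form. If most participants report every dose, the named adherence summary is the same for any non-adherent share below about a quarter: 5% and 24% both read 100% (100–100), with means 7.6 points apart (98.0% − 90.4%) when non-adherers take 60% of doses. If the majority instead miss occasional doses, the summary responds, but weakly.

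The conclusion rests on the bound, which the article states, and on clustering at or near it, which is assumed. It concerns one secondary descriptive table, in participants who opt in to adherence monitoring. It does not extend to the planned regression, to EQ-5D-5L or to cost-effectiveness, and the primary endpoint is untouched. Severity is minor.

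**What to change.** Keep the median (IQR). In the SAP and table shells add, by the same subgroups (genotype, cirrhosis status, prescribed treatment):

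1. the percentage of participants below dose thresholds fixed before the data are examined (for illustration, below 100%, 95% and 80% of prescribed doses; the article gives no basis for particular cut-points, so the choice should be justified in the SAP);
2. the mean proportion of prescribed doses taken, with a 95% interval.

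The weekly dose counts already collected are sufficient, so no new data are needed. The cost is a few extra columns and the need to choose cut-points in advance. Small cells will come under the article's own rule of reporting frequencies below five as <5, and the percentages should be presented so that they do not undo it.

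Optionally, the mean EQ-5D-5L index could be reported beside its median. That is a suggestion, not a correction.
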